### Criteria for discontinuing or modifying allocated interventions *{11b}*

Criteria for discontinuing the allocated interventions are:Patient withdrawal of consent at any point of the studyWorsening mental health or psychological well-being of the patient such as the onset of severe mental illness as diagnosed by a hospital psychiatristSignificant deterioration of patient’s physical health and/or death

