### Strategies to improve adherence to interventions *{11c}*

All participants for this trial will be eligible to receive the psychological and breathing interventions (see the ‘Intervention description {11a}’ section). Those in the treatment arm of the study will be offered the intervention immediately after enrolment and those in the control arm of the study will have the option of completing the group programme once the study period has been completed. Additional measures to aid adherence include its virtual format, ensuring there are no geographical barriers precluding someone from participating. Moreover, the group sessions will only last approximately 90 min, inclusive of a break, to minimise the content burden. All participants will also be well-informed during the consent process. The study participation burden, such as completion of primary outcome questionnaires at t(0) (baseline), t(1) (post-6-week group intervention) and t(2) (3 months post-intervention period), post-enrolment will be explained. The research assistant responsible for screening potential study participants will record all eligible candidates and those that do not proceed with the study due to ineligibility, non-consent or withdrawal. In so far as it is possible, only eligible and fully willing individuals will proceed to randomisation and allocation of the patient to either the CFT and BPR or control groups.

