#### Plans to promote participant retention and complete follow-up *{18b}*

During the screening process, study candidates will receive information about the study in the form of a study ‘ad’ and an extensive participant information leaflet describing the study in detail. Study candidates will have ample opportunity to ask questions about the study, at all stages of participation. Eligible candidates will be encouraged to enrol only if they are willing and able to commit to the 18-week study period (6-week intervention plus 12-week follow-up). Every effort will be made by the research assistant to remain in contact, as deemed appropriate, with all study participants throughout their participation. Participants will also have the contact details of the research team should they wish to make contact outside of other study contact points.

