### Statistical methods

#### Statistical methods for primary and secondary outcomes *{20a}*

Outcome analyses will be performed by a dedicated biostatistician. An intention-to-treat analysis will be performed on all randomised patients and a per-protocol analysis will be performed on all patients who complete the study. Descriptive statistics will be calculated for all outcome measures at each time point. Continuous variables will be reported using means, medians, standard deviations and score ranges. Categorical variables will be described using frequencies and percentages.

Descriptive and inferential statistics will be obtained using the appropriate statistical methods that seek to address our identified objectives. The primary analysis will compare the effect of the interventions on the primary outcome; distress levels at 12 weeks post-completion of the intervention period (i.e. c18 weeks post-baseline). All outcome analyses will be conducted according to an intention-to-treat principle, i.e. all randomised participants will be included in the main analysis and will be analysed as randomised, regardless of protocol adherence. Secondary analysis will include the analysis of the primary outcome post-intervention and analysis of the secondary and treatment process outcomes detailed previously post-intervention and at the 12-week follow-up. Linear mixed models on the outcome measures over time will be fitted to evaluate the effect of both study conditions, which intrinsically adjusts for baseline scores.

Statistical significance will be assessed from a *p* value < 0.05 from the group by time interaction term. For all tests, two-sided *p* values will be used, which will be reported to four decimal places with *p* values < 0.001 reported as *p* < 0.001. The Bonferroni method will be used to appropriately adjust the overall level of significance for multiple secondary outcomes as applicable. In the case of a significant result, planned contrasts of the group effects at the post-treatment period and at the 12-week follow-up will be used to investigate the direction and pattern of effects and outlined in advance in the SAP. As a key component of the reporting of the analyses of outcomes, the mean changes (irrespective of statistical significance) and correlations of the measures between the assessment time periods will be obtained. SPSS will be used to conduct the analyses.

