### Methods in analysis to handle protocol non-adherence and any statistical methods to handle missing data *{20c}*

Careful attention will be paid to ensure that all participants are fully assessed at all three study time points to minimise missing data. The study’s research assistant will seek to enter hard copy data to the REDcap database in a timely manner, once time point data is collected. This will provide an opportunity for identification of any missing data, which the research assistant will follow up on by encouraging study participants to try and complete any missing answers. We do not plan to use additional statistical methods such as multiple imputation as studies have demonstrated that linear mixed modelling is mostly sufficient to control for missing data [31, 32]. However, multiple imputation will be considered for any measure with over 5% missing data, using a chained equations method robust to non-normally distributed data. This will be fully reported in line with the updated Consolidated Standards of Reporting Trials (CONSORT) recommendations [33].

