### Adverse event reporting and harms *{22}*

The study interventions associated with this trial do not involve any physical interventions, and all patients will receive standard of care during their study participation period. Therefore, it is not expected that any participants that volunteer to take part in this trial will suffer from any physical complications as a consequence of participation in this study. However, it is possible that some participants may find the study interventions (psychological therapy, mindfulness and breathing) distressing. This is not expected, but in the event anything arises which is out, it will be reported to the principal investigator. The participant will be removed from the trial if merited and further support will be provided.

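### The harms section removes a participant distressed by the intervention from the trial rather than from the intervention only, which could cost 18-week scores in the treated arm alone

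*Protocol article*

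**What the plan says.** All references are to the protocol article.

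- **Harms {22}.** The section accepts that "it is possible that some participants may find the study interventions (psychological therapy, mindfulness and breathing) distressing". It adds that this is not anticipated, and that such events go to the principal investigator. It then states: "The participant will be removed from the trial if merited and further support will be provided".
- **Discontinuation {11b}.** Worsening mental health or psychological well-being appears under "Criteria for discontinuing the allocated interventions", so the consequence named there is stopping the intervention.
- **Post-trial care {30}.** Stress arising from the intervention, during or after the trial, leads to an offer of further psychological management by a psychologist outside the trial. Removal is not mentioned.
- **Adherence {11c}.** During the study period only the treated arm gets the programme; "those in the control arm of the study will have the option of completing the group programme once the study period has been completed".
- **Analysis {20a}.** In the main analysis "all randomised participants will be included in the main analysis and will be analysed as randomised, regardless of protocol adherence". In addition, "a per-protocol analysis will be performed on all patients who complete the study".
- **Retention {18b}.** The research assistant will try to "remain in contact, as deemed appropriate, with all study participants throughout their participation".
- **Missing data {20c}.** The aim is full assessment at all three time points. No imputation is planned by default, on the ground that "linear mixed modelling is mostly sufficient to control for missing data"; multiple imputation is considered for a measure with more than 5% missing.

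**The concern.** Stopping a treatment and leaving a trial are different events. Section {22} prescribes the second where {11b} and {30} need only the first.

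The trigger in {22} is distress caused by the intervention. Before week 18 that can arise only in the treated arm. It is also close to what the primary outcome measures, so those removed would tend to be treated patients who are doing badly. Comparable controls have no such exit. If their t1 and t2 scores are not collected, the treated mean at 18 weeks improves for a reason unrelated to efficacy.

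The planned analysis would not fully correct this. The mixed model and multiple imputation both assume that, given the observed data, missingness does not depend on the unseen score. Here it may. The per-protocol analysis, restricted to completers, would drop the same patients. The result at stake is the primary comparison, which the Background section links to a possible national roll-out.

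**Working it through.** **Inputs from the document (Sample size {14}).** Target difference 1 unit, SD of change 2 units, two-sided 5% level, 80% power, 64 per group, 80 after 20% attrition. These reproduce: the two-sample t-test needs 63.77 per group, rounded up to 64, and 64/0.8 = 80. This point does not affect the sample size.

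**Assumptions, because the document gives no figure.** The number removed, and how strongly the removal trigger is related to the 18-week change. True mean change is taken as −1 in the treated arm and 0 in controls.

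**Step 1: simple means, fixed outcome for those removed.** Let f be the fraction of the treated arm removed and m the mean change those patients would have shown. The retained mean is (−1 − f·m)/(1 − f), so benefit is overstated by f(m + 1)/(1 − f). Suppose they would have worsened by 2 or 3 units:

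- 1 of 80: 0.0125 × 3/0.9875 = 0.038; 0.0125 × 4/0.9875 = 0.051.
- 2 of 80: 0.025 × 3/0.975 = 0.077; 0.025 × 4/0.975 = 0.103.

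**Step 2: simple means, selection through a correlated trigger.** If the trigger correlates r with the 18-week change, m + 1 = 2·r·φ(z)/f, where z is the normal quantile at 1 − f. The overstatement is 2·r·φ(z)/(1 − f).

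| Removed of 80 | z | φ(z) | r = 0.5 | r = 1 |
|---|---|---|---|---|
| 1 | 2.241 | 0.0324 | 0.033 | 0.066 |
| 2 | 1.960 | 0.0584 | 0.060 | 0.120 |
| 4 | 1.645 | 0.1031 | 0.109 | 0.217 |
| 8 | 1.282 | 0.1755 | 0.195 | 0.390 |

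The r = 1 column is a bound: it supposes that exactly the worst 18-week responders are identified in advance.

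**Step 3: the planned type of model.** A simulation of the t2 group-by-time contrast used an unstructured covariance (assumed baseline SD 1.8, correlation 0.6 between t1 and t2 change, −0.4 between baseline and change). Each range runs from r = 0.5 to r = 1.

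| Removed of 80 | Lost before t1 | Lost after t1 |
|---|---|---|
| 2 | 0.048 to 0.098 | 0.036 to 0.072 |
| 4 | 0.088 to 0.180 | 0.064 to 0.134 |
| 8 | 0.163 to 0.329 | 0.119 to 0.246 |

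The model reduces the bias, more so when a t1 score exists, but does not remove it. Multiple imputation gives 0.091 to 0.178 for 4 lost before t1 and 0.168 to 0.330 for 8, essentially no change. One or two removals would not by themselves reach the 5% threshold in {20c}: 2/160 = 1.25%.

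**Step 4: false-positive rate.** With no true effect, 2 of 80 removed and a t-test on the remaining patients, the chance of a significant result favouring the intervention rises from 2.5% to between 3.7% (r = 0.5) and 6.0% (r = 1). This is a completer test, not the planned model.

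If removed patients are still assessed at t1 and t2, the bias from this rule is zero.

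**The case against.** Section {22} is a harms statement, not an analysis rule. It deletes no data, excludes nobody from analysis and does not say that assessment stops. Removal depends on a judgement that it is warranted, and the event is described as unlikely. Section {11b} itself lists withdrawal of consent and death among reasons to discontinue the intervention, so the authors may not have separated leaving treatment from leaving the trial. The retention wording in {18b} does not say when participation ends. The article condenses a fuller protocol that may be clearer. Being upset by a session in weeks 1 to 6 is also not the same as a high score at week 18, particularly in patients who then receive extra support.

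Most of this stands, and it limits the point. A reader might infer that {22} directly contradicts the intention-to-treat commitment in {20a}. The document does not support that: a removed patient's baseline, and any t1 score, can still enter the mixed model. The tension is about follow-up that may be lost, not about exclusion from analysis. A reader might also infer a serious threat to the primary result from the 8-of-80 or r = 1 figures. These are extreme assumptions for an event the authors do not expect.

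What the objection does not remove is the sentence itself. It is a stated rule of conduct rather than a detail left out, its ordinary meaning is that participation ends, and no section says follow-up continues afterwards. No later analysis plan can recover scores that were not collected.

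**Conclusion.** The point holds as a flaw in wording with a small likely effect. Followed in its ordinary sense, {22} can lose t1 and t2 scores in the treated arm only, for a reason tied to the primary outcome. That undercuts the intention-to-treat aim of {20a} and the complete-assessment aim of {20c}, in a direction that favours the intervention.

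The size rests wholly on assumptions about how many are removed and how selectively. With 1 or 2 of 80 removed, the benefit is overstated by up to about 0.1 unit against the 1-unit target. With 4 removed, the mixed-model figure is roughly 0.06 to 0.18. Larger values need removals to be far more common than the protocol anticipates. If the sponsor already intends follow-up to continue, there is no bias, and only the sentence needs correcting.

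**What to change.** In {22}, replace the removal sentence with wording such as:

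> The participant will stop the intervention if merited, will be offered further support, and will continue the t1 and t2 assessments unless they withdraw consent to follow-up; they remain in the intention-to-treat analysis.

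This brings {22} into line with {11b}, {30} and {20a}. It needs no extra patients, visits or instruments. The cost is a few additional follow-up contacts with distressed patients, some of whom may decline. Section {25} already provides the amendment route, and Trial status reports 8.5% recruited, so a change at that stage would cover nearly all participants.

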### Frequency and plans for auditing trial conduct *{23}*

A third-party researcher, affiliated with the UCD clinical research centre, but not involved in the trial in terms of patient recruitment, data collection, data entry and analysis will undertake an auditing process for trial conduct. This will occur every 6 months and will include the following: exploring the REDCap database for accuracy, spot check verification of data entry, screening for duplicate data and ensuring ongoing adherence to data protection guidelines.

### Plans for communicating important protocol amendments to relevant parties (e.g. trial participants, ethical committees) *{25}*

This is not anticipated but should the research group seek to modify any aspect of the research protocol, approval for any such amendments will be sought from the relevant IRB. Participant information leaflets will be updated accordingly and any changes to the published protocol will be reported in full in any future publications.

### Dissemination plans *{31a}*

The intention of the research team is to disseminate the results from this clinical trial in several ways. These will include local talks to various professional audiences at the clinical site of the research project. The plan also includes publication in an international peer-reviewed journal and by way of oral and/or poster presentations at national and international scientific meetings. Positive findings will be reported in full along with potential robust findings of equivalence.

## Discussion

This paper describes the protocol of the COMFORT trial, a RCT comparing the effectiveness of an online, group-based, compassion-focussed therapy (CFT) psychological intervention combined with breathing pattern retraining (BPR), to those receiving standard medical care only, at reducing psychological distress in adults experiencing cancer recurrence during COVID-19. We have endeavoured to enhance the quality of research in the area of hospital-based, psycho-oncology, particularly as it continues to develop in the Irish context. The inclusion criteria for the study are relatively broad, in an effort to capture a representative sample and with the aim of maximising the generalisability of the findings.

There are a number of limitations inherent in this trial, most prominently the inability to blind study participants and clinicians to treatment allocation. We have attempted to address issues of additional biases as far as has been practically possible through the provision of randomisation and concealment of allocation, strategies to minimise and manage incomplete outcome data, the delivery of a specialist combined intervention by an experienced senior psychologist specialising in psycho-oncology and BPR, the recruitment of an adequate sample size and having appropriate duration of follow-up and a priori specification of all primary and secondary outcomes as detailed in this study protocol. We have also traded the reported downside of a virtual group (reduced social interaction with and support from fellow peers) off against this platform removing a potential geographical boundary for some individuals unable to commute to Dublin on a regular basis.

To our knowledge, this will be the first RCT to assess the effectiveness of a combined psychological and breathing pattern retraining intervention for cancer recurrence. The study results will add to current knowledge in the field of psycho-oncology and general cancer management and will have the potential to inform the delivery of best-practice treatments for cancer patients.

### Trial status

The trial is registered on ClinicalTrials.gov Identifier: NCT05518591. The current protocol is version 2 of 05 February 2021. Participant recruitment began on 25 August 2022, and full patient recruitment is estimated to be completed by September 2023. Currently, 8.5% of patients have been recruited.

ClinicalTrials.gov. Registered on 25 August 2022. All items from the World Health Organization Trial Registration Data set have been included.

## Data Availability

The final trial dataset generated from this study will be made available from the corresponding, first and/or principal authors upon reasonable request.

## Abbreviations

FOR: Fear of recurrence
MMUH: Mater Misericordiae University Hospital
NCCN: National Comprehensive Cancer Network
DT: Distress Thermometer
CFT: Compassion-focussed therapy
CBT: Cognitive behavioural therapy
BPR: Breathing pattern retraining
RCT: Randomised control trial
HSE: Health Service Executive
PHQ: Patient Health Questionnaire
DSM-IV: Diagnostic and Statistics Manual, Fourth Edition
GAD: Generalised anxiety disorder
IES-R: The Impact of Event Scale-Revised
Mini-MAC: Mini-Mental Adjustment to Cancer
PIL: Participant information leaflet
REDcap: Research electronic data capture
CRF: Case report form
SAP: Statistical Analysis Plan
CONSORT: Consolidated Standards of Reporting Trials
DPIA: Data Protection Impact Assessment
DPO: Data protection officer
UCD: University College Dublin
